#### Baseline

Baseline characteristics will be compared among the different groups using chi-square tests or Fisher exact tests for comparison of proportions and Mann-Whitney *U* tests for comparison of means.

#### Hypotheses 1, 6, and 7

Total weekly alcohol consumption and frequency of heavy episodic drinking are likely to be skewed and overdispersed, and we will, therefore, analyze both using negative binomial regression. Classification as a risky drinker will be analyzed using logistic regression. Both unadjusted and adjusted regression models will be created. Adjusted models will include baseline values of the respective outcome measures and responses to the baseline questions regarding sex, civil status, age, motivation, importance, and know-how. As alcohol consumption differs significantly among age groups, and possibly also the effect of the intervention, multilevel models will also be created in which slopes are allowed to vary among age groups. Effect modification tests will be performed in all models to assess if any of the baseline characteristics moderate the effect of the intervention. The adjusted models will be the primary models.

#### Hypothesis 2

Mediators will be explored using a causal inference framework [60], where Monte Carlo methods are relied upon for inference. This allows for any type of model (linear and nonlinear) to be used to represent the relationships between the group allocation, mediating variable, and outcome. A total of 4 models will be created for each outcome measure, 3 that investigate the mediating factors on their own and a fourth that incorporates all mediators at once. If any baseline characteristics were found to moderate the effect in the primary analysis, then additional mediator models will be created to include these as moderators.

#### Hypotheses 3 and 4

Whether or not individuals decided to give informed consent will be regressed against group allocation (Consent-1 and Consent-2) using logistic regression. Adjusted regression models will be explored that include baseline characteristics (including only participants who gave informed consent). Differences among the 2 groups on responses to the recall questionnaire will be investigated using chi-square tests or Fisher exact tests for comparison of proportions.

#### Hypothesis 5

Whether or not individuals requested more information by pressing the hyperlinks will be regressed against both group allocation (Info-1 and Info-2) and fixed responses to the control group experience questionnaire using logistic regression. Adjusted models will be explored that include baseline characteristics. Differences among the 2 groups on responses to the control group experience questionnaire will be investigated using chi-square tests or Fisher exact tests for comparison of proportions.

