Young adults were also randomized in a third study of an SMS-based intervention, drawing its study population (n=765) from emergency department patients at 4 hospitals in Pittsburgh (United States) [26]. One group was given an intervention, which asked them to respond to drinking-related questions and receive feedback through SMS each Thursday and Sunday; another group was asked to respond to drinking-related questions on Sundays only and without feedback; and a control group was not sent any SMS. At 3-month follow-up, 78.0% (597/765) of randomized participants responded, and those who were lost-to-follow-up were more likely to be African American, not currently enrolled in college, and with a baseline higher number of episodes of heavy drinking. Thus, although the trial did identify a significant difference between the participants that received an SMS on Thursdays and Sundays compared with the control who received nothing (drinks per drinking day: incidence rate ratio=0.86, 95% CI 0.79 to 0.94; no *P* value reported), these results should be viewed with some skepticism given the systematic loss to follow-up.

Finally, a pilot study conducted among risky drinkers seeking treatment on the Web suggested that delivering motivational SMS messages daily rather than weekly reduced consumption [27]. Although the study was a pilot, the recruitment of 661 eligible participants over an 8-month period was encouraging.

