#### Recruitment and Eligibility

Using Web search engine advertisements (Google, Yahoo, and Bing) and social media (Facebook), we will target individuals in the general population of Sweden seeking help to reduce their alcohol consumption (advertisements are shown in Figure 2). Participants will initially be recruited over a 6-month period. Additional 6-month periods will be added if not enough participants have been recruited according to the initial power calculation. If 20.03% (426/2126) or less of the required population has been recruited at 12 months, then recruitment will stop at this time and data will be analyzed to inform future trial design. Recruitment will stop after 24 months if not before.

Individuals interested in participating in the study will be asked to send an SMS message with a specific code to a dedicated phone number. Within 10 min, participants will receive an SMS with a hyperlink that takes them to a Web page asking for informed consent. Individuals will be randomized to 1 of 2 different means of presenting the trial procedure when asking for informed consent (Consent-1 and Consent-2). Please see Multimedia Appendix 1 for more details.

All individuals giving informed consent will be asked to complete a baseline questionnaire, which will also assess eligibility for the trial. The inclusion criteria will include the following: aged 18 years or older, ownership of a mobile phone, and being classified as a risky drinker according to Swedish guidelines.

Note that there is no upper limit to alcohol consumption as an exclusion criterion, meaning the study population is anticipated to comprise both harmful (ie, individuals who have experienced harm from any level of consumption [48]) and hazardous drinkers (ie, individuals with a consumption pattern that suggests increased risk to health [48]). No additional support will be offered to individuals who have a very high-consuming behavior.

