### Measures

All questions asked at baseline and subsequent follow-ups can be found in Multimedia Appendix 3.

For hypotheses 1, 6, and 7:

Primary outcome measures: Total weekly alcohol consumption and frequency of heavy episodic drinking.Secondary outcome measures: Classification as risky drinker according to Swedish guidelines.

For hypothesis 2:

Mediation measures: Confidence in one’s ability to reduce consumption, importance of reducing, and knowledge of how to reduce consumption.

For hypotheses 3 and 4:

Primary outcome measures: Enrollment rates from each study conditionSecondary outcome measures: Recall of trial procedures measured through a series of questions.

For hypothesis 5:

Primary outcome measures: Rates of additional information being requested by pressing on the supplied hyperlink.

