**Figure 3 figure3:**
[figure not shown]
Standard Protocol Items: Recommendations for Interventional Trials figure.

Total weekly alcohol consumption will be assessed by asking participants the number of standard units of alcohol they consumed last week, that is, a short-term recall method [55]. Using a summary measure, rather than asking day-by-day, will allow for the same question to be asked, regardless if responses are collected via Web questionnaires, SMS, or by phone interviews (see Follow-up Attempts). In addition, 1 study suggests that when considering short-time spans, summary measures do not imply any noteworthy bias compared with asking for consumption day-by-day [56]. The frequency of heavy episodic drinking will be assessed by asking participants how many times they have consumed more than 4 (females) or 5 (males) standard units of alcohol on 1 occasion the past month, again asking for a summary measure over a concrete time period. An individual is classified as a risky drinker if either total weekly consumption or heavy episodic drinking exceeds recommendations.

Confidence, importance, and know-how will be measured at baseline and at 1-month follow-up by asking “How confident are you that you will be able to reduce your alcohol consumption?,” “How important do you think it is to reduce your alcohol consumption?,” and “How well do you know how to reduce your alcohol consumption?,” all 3 with response options on a 10-point scale (see Multimedia Appendix 3). The wording of the questions at 2- and 4-month follow-up will change to include those who have reduced their consumption: “How confident are you that you will be able to reduce or keep a lower level of alcohol consumption?,” “How important do you think it is to reduce or keep a lower level of alcohol consumption?,” and “How well do you know how to reduce or keep a lower level of alcohol consumption?.”

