### Statistical Analysis Methods

All analyses will be done under the intention-to-treat principle, where all randomized individuals will be included. Missing outcome data will initially be handled by a complete-case analysis, which assumes that data are missing at random (MAR). If data are systematically missing, then it may be the case that early responders differ from late responders and, in extension, that late responders are more similar to nonresponders. We will, therefore, explore the plausibility of the MAR assumption by regressing the primary outcomes on the number of follow-up attempts needed before a response was recorded. To further explore the MAR assumption, attrition will be investigated among study groups by comparing baseline characteristics between those who did and did not respond at follow-up. A sensitivity analysis that includes imputed values for missing outcome data (using multiple imputation by chained equations [58]) will also be performed. Data will be graphically examined for outliers or data input errors, and sensitivity analyses will be performed excluding any erroneous data points.

For all models, coefficients of interest will be assessed for statistical significance using a null hypothesis testing approach, where tests will be 2-tailed at the .05 significance level. Alongside the null hypothesis tests, posterior distributions using a Bayesian approach will be calculated for each coefficient. Both significance tests and posterior distributions will create a basis for scientific inference [59].

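### Each primary adjusted model carries only its own outcome's drinking baseline; adding the other one, already collected for eligibility, is a nearly free improvement

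*Protocol article*

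**What the plan says.** Measures names two primary outcomes for the main hypothesis: "Primary outcome measures: Total weekly alcohol consumption and frequency of heavy episodic drinking". Risky-drinker status is secondary. The two counts are analysed by negative binomial regression and the classification by logistic regression.

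Under Hypotheses 1, 6, and 7 the covariates are stated: "Adjusted models will include baseline values of the respective outcome measures and responses to the baseline questions regarding sex, civil status, age", followed by motivation, importance and know-how. The same paragraph says "The adjusted models will be the primary models". So this is a fixed choice in the document and not a detail left open.

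Both drinking measures should be in hand before randomization. Recruitment and Eligibility says "All individuals giving informed consent will be asked to complete a baseline questionnaire, which will also assess eligibility for the trial", and Measures says "An individual is classified as a risky drinker if either total weekly consumption or heavy episodic drinking exceeds recommendations". The questionnaire itself (Multimedia Appendix 3) is not shown, so this is inferred from the eligibility rule.

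On missing outcomes, Statistical Analysis Methods starts from complete cases under missing at random. It adds a regression on the number of contact attempts, a baseline comparison of responders and nonresponders, and multiple imputation as a sensitivity analysis.

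**The concern.** Weekly consumption is one recalled week, whereas HED is counted over the past month. A person can qualify on HED alone after a light week. For that person the weekly model's only drinking covariate says little, and the more informative one is left out.

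The same wording has a sharper effect on the risky-drinker model. Everyone must be a risky drinker to enter, so the baseline value of that outcome is constant and drops out. Read literally, the model then adjusts for six other characteristics and no drinking measure.

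A complete-case analysis is protected against selective loss only through the covariates in the model. The protocol's own background (Short Message Service–Based Interventions) reports an SMS alcohol trial whose lost participants were more likely to be people "with a baseline higher number of episodes of heavy drinking", and it treats that trial's result with caution for this reason. The weekly-consumption model does not condition on that variable. What is at stake is some precision in all three models and the credibility of missing at random in one.

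**Working it through.** **1. The plan's own figures.** The inputs are from Power Calculation: reduction beta (mean 0.15, SD 0.025); control mean normal (10, SD 0.5); intervention mean normal around (1−γ) times the control mean (SD 0.5); θ normal (1, SD 0.05); 1:1 binomial allocation; two-sided 0.05. Re-running this with 1800 analysed gives power 0.790 by simulation (20,000 runs) and 0.791 analytically, against the stated 0.79. For loss, averaging 1800/r − 1800 over a beta with mean 0.85 and SD 0.05 gives 325 (interquartile range 231 to 398), against the stated 326 (231 to 398). The calculation uses no covariates, so the covariate choice cannot make it wrong.

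**2. Precision, analytic.** Fix the inputs at means 10 and 8.5, with 900 per arm and residual dispersion a:

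SE² = (1/10 + a)/900 + (1/8.5 + a)/900

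With a = 1, SE = √(2.2176/900) = 0.0496 and power is 0.906. This exceeds 0.79 because the plan also draws its inputs at random. Suppose the other drinking baseline explains an extra share s of the dispersion, so that a = 1 − s. The values of s are assumptions.

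| s | SE | change in SE | equivalent analysed N | power |
|---|---|---|---|---|
| 0.02 | 0.0492 | −0.9% | 1833 | 0.911 |
| 0.05 | 0.0485 | −2.3% | 1885 | 0.918 |
| 0.10 | 0.0473 | −4.6% | 1978 | 0.930 |
| 0.15 | 0.0462 | −7.0% | 2082 | 0.941 |

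For s = 0.05, equivalent N = 1800 × 2.2176/2.1176 = 1885.

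**3. Precision, simulated.** Assumptions: 2126 randomized, about 14% lost, correlation 0.5 between the two baselines, and log-rate slope 0.1, 0.2 or 0.3 per SD of the other baseline. The SE falls by 0.7%, 2.7% and 5.6%.

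A second simulation set own baseline on the raw scale to variance 1. Own baseline on the log scale gave 0.961 to 0.963, and both baselines on the log scale gave 0.936, 0.916 and 0.899. The added covariate alone is therefore worth 0.936/0.962 = 0.973 to 0.899/0.962 = 0.935 in variance, or about 1.4% to 3.3% in SE.

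**4. Attrition, weekly-consumption model.** Same set-up as the first simulation in step 3, with true rate ratio 0.85. The dropout slope is on the logit scale per SD of baseline HED.

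| Loss linked to HED | HED slope on outcome | own baseline only | both baselines |
|---|---|---|---|
| equal in both arms, 0.5 | 0.1 / 0.2 / 0.3 | 0.852 / 0.850 / 0.852 | 0.852 / 0.850 / 0.851 |
| one arm only, 0.25 | 0.1 / 0.2 / 0.3 | 0.850 / 0.844 / 0.845 | 0.852 / 0.848 / 0.851 |
| one arm only, 0.5 | 0.1 / 0.2 / 0.3 | 0.847 / 0.844 / 0.835 | 0.851 / 0.853 / 0.849 |

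In SE units the last row is ln(0.851/0.847)/0.0442 = 0.1, ln(0.853/0.844)/0.0451 = 0.2 and ln(0.849/0.835)/0.0468 = 0.4. Opposite dropout slopes in the two arms, an extreme case, gave 0.827 against 0.848, about 0.5 SE.

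**The case against.** The strongest reply is that own-outcome baseline plus six further covariates, prespecified and named as primary, is a conventional and valid set. That stands: nothing here contradicts the rest of the protocol. It could also be said that the plural in the covariate sentence was meant to cover both measures in every model. If so, the sentence is unclear and the same edit settles it.

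A reader might infer a larger precision loss. Comparing both baselines on the log scale with own baseline on the raw scale gives 6% to 10% lower variance, or 120 to 200 participants. But the protocol does not say on which scale the baselines enter, so the scale part of that gain cannot be charged to the plan. The simulations also omit the six other covariates, and any overlap with HED would shrink the gain. In the second simulation, the empirical variance in one scenario was 0.981, which is about no gain over the log scale alone.

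A reader might also infer that HED-linked loss biases both primary analyses. The documents do not support this. The HED model already conditions on baseline HED. Equal HED-linked loss caused no shift in the weekly-consumption model; bias needs loss that differs by arm, or HED that also modifies the effect. The cited trial's loss is not reported by arm. Arm-specific loss is still possible, because participants know their allocation and a Swedish app trial cited in Mobile Phone Apps lost 22.7% to 39.1% across groups.

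The planned imputation covers part of this, but only as a sensitivity analysis. The comparison of responders with nonresponders can reveal a problem but corrects nothing.

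**Conclusion.** The point holds as a free improvement to the covariate set. Each primary model leaves out a drinking baseline that the trial should already have, and the adjusted risky-drinker model, read literally, has none. The gain from adding the other measure is about 1% to 3% of the SE under plausible assumptions and about 7% at the extreme. For the weekly-consumption model it also removes a shift of about 0.1 to 0.5 SE in constructed scenarios where HED-linked loss differs by arm. The correlations, outcome slopes and dropout slopes behind these ranges are assumptions; the documents give none. The planned analysis is not invalid.

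**What to change.** In Hypotheses 1, 6, and 7, replace the reference to the respective outcome's baseline with a statement that every adjusted model for these hypotheses includes both baseline weekly consumption and baseline HED frequency, with the other covariates already listed. This covers the two negative binomial models and the logistic risky-drinker model. In Statistical Analysis Methods, state that the imputation model includes both as well.

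Optionally, state the scale: log(1+x) suits skewed counts in a log-link model with no upper limit on consumption at entry.

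The cost is one or two sentences and one extra covariate in each primary model (two in the risky-drinker model), which is negligible at about 1800 analysed. No new data are needed. The change should be fixed before outcome data are examined by arm, because the Randomization section says the analyst cannot be blinded.

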#### Intervention and Control Conditions

Eligible individuals will be randomized to either an intervention group or a control group (intervention and control). The intervention group will receive the novel intervention for 4 months and will also be recommended to read about alcohol, health, and society on the same website as the control group (see Multimedia Appendix 2). Participants allocated to the control group will be advised that they will go through an initial phase of 4 months during which they are to receive information to increase their motivation and reduce their consumption, after which they will be given access to the new support tool. Thus, individuals allocated to the control setting will be given access to the novel intervention after completion of the final follow-up (4 months after randomization); no further data will be collected from individuals in the control setting.

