**Exploratory Hypotheses**
6. Alcohol consumption will differ between groups Consent-1 and Consent-2 at 2 and 4 months after randomization. The 2-month interval will be primary.7. Alcohol consumption will differ between groups Info-1 and Info-2 at 2 and 4 months after randomization. The 2-month interval will be primary.

With regard to recall of trial procedures, there are 3 parameters that are of interest. First, participants will be asked if they recall receiving information about allocation to 2 different groups. As information regarding group allocation was presented identically for Consent-1 and Consent-2, this question will both work as a check that randomization succeeded and as a general baseline for recall regardless of group allocation. Second, participants will be asked if they recall how personal data will be handled in the study and their rights to these data. Finally, participants will be asked if they remember how the data would be analyzed and results communicated (see Multimedia Appendix 3).

We wish to measure if participants access further health-related information after reading a short SMS with basic information about short-term and long-term consequences of alcohol consumption. A proximal outcome of this is to measure whether or not participants in Info-1 and Info-2 request more information by following the included hyperlink. In addition, a short questionnaire at 4-month follow-up will investigate the control group participants, which will be used to investigate further differences between Info-1 and Info-2 (see Multimedia Appendix 3).

The acceptability and usability of the intervention will be measured through a questionnaire and the system usability scale [57] at 4-month follow-up (see Multimedia Appendix 3). The system usability scale comprises 10 Likert items exploring users’ perception on usability of a product or service.

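### For exploratory hypothesis 6, the primary model adjusts for answers given after randomization to the consent mode, and the contrast is between enrolled groups, not intention-to-treat

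*Protocol article*

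**What the plan says.** Recruitment and Eligibility sets the order of events. At the consent page, "Individuals will be randomized to 1 of 2 different means of presenting the trial procedure when asking for informed consent". After that, "All individuals giving informed consent will be asked to complete a baseline questionnaire, which will also assess eligibility for the trial". Intervention and Control Conditions then randomizes eligible people to the two trial arms, and controls are further split into Info-1 and Info-2.

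The exploratory hypotheses include number 6: "Alcohol consumption will differ between groups Consent-1 and Consent-2 at 2 and 4 months after randomization". The 2-month time point is named as primary.

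Statistical Analysis Methods, under Hypotheses 1, 6, and 7, gives all three hypotheses one analysis. "Both unadjusted and adjusted regression models will be created". On the covariates: "Adjusted models will include baseline values of the respective outcome measures and responses to the baseline questions regarding sex, civil status, age", followed by motivation, importance and know-how. Then: "The adjusted models will be the primary models". No exception is made for hypothesis 6. The opening of the same section applies intention-to-treat to every analysis, with everyone randomized included.

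**The concern.** A covariate is safe to adjust for when the randomized exposure cannot have changed it. The word baseline gives that assurance for the trial arms and for the Info groups, because the questionnaire comes first. For the consent mode it does not, because respondents have just read one of the two texts being compared.

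Three kinds of answer are involved:

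- **Sex, age and civil status.** The consent text cannot plausibly change these.
- **Motivation, importance and know-how.** The text could change these. The Mediation section treats importance and know-how as routes by which behavior changes. Adjusting for them can remove a real effect.
- **Baseline drinking.** The text cannot change drinking that has already happened, but it could change how candidly it is reported.

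There is also a question of who is compared. People who decline, or who are ineligible on their answers, have no follow-up. Hypothesis 3 itself expects enrollment to differ by consent mode. The hypothesis 6 contrast is therefore conditional on events after its own randomization, whichever covariates are used.

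**Working it through.** **1. Order of events for each hypothesis (from the Design section)**

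| Hypothesis | Contrast | When randomized | Questionnaire answered |
|---|---|---|---|
| 1 | Intervention vs control | After eligibility is known | Before randomization |
| 7 | Info-1 vs Info-2 | Within the control group | Before randomization |
| 6 | Consent-1 vs Consent-2 | At the consent page | After randomization and exposure |

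The problem is confined to hypothesis 6.

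**2. The plan's own figures.** The protocol gives no effect size or power for hypothesis 6. Its main-trial figures reproduce: average power 0.791 at N=1800 (stated 0.79) and expected loss 325 (stated 326). They do not bear on this point. All inputs below are assumptions.

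**3. How much adjustment removes.** Let C be the consent mode and X a questionnaire answer, with X = u + s·C. Let the log follow-up mean be a + d·C + b·X. The total effect is T = d + b·s, and the share carried by the answer is p = b·s/T. A model without X estimates T. A model with X estimates d = (1 - p)·T.

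With T = -0.10, b = 0.6, SD of u 0.6, intercept a = 2.2 and negative binomial counts (gamma shape 1.5), averaged over 6 simulated data sets of 40,000:

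| Share p | Expected adjusted, (1 - p)·T | Simulated unadjusted | Simulated adjusted |
|---|---|---|---|
| 0% | -0.100 | -0.101 | -0.101 |
| 25% | -0.075 | -0.096 | -0.070 |
| 50% | -0.050 | -0.099 | -0.050 |
| 75% | -0.025 | -0.096 | -0.021 |
| 100% | 0.000 | -0.096 | 0.003 |

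The loss equals the share carried by the answers, and that share is unknown.

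**4. Motivational answers.** In a separate check on assumed inputs, a genuine effect of -0.05 became 0.00 once these answers were adjusted for.

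**5. Baseline drinking under a pure reporting shift.** Suppose one text lowers reported drinking by 10% at both times. If follow-up depends on baseline with slope b on the log scale, the adjusted reduction is 1 - 0.9^(1 - b): 6.1%, 5.1% and 4.1% for b = 0.4, 0.5 and 0.6. Simulated with n=1800, two assumed between-person variances and 200 trials each:

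| Eligibility cut | Without baseline | With baseline | Removed |
|---|---|---|---|
| None | -0.110 | -0.071 | 0.039/0.110 = 35% |
| None | -0.104 | -0.057 | 0.047/0.104 = 45% |
| More than 9 reported units | -0.073 | -0.052 | 0.021/0.073 = 29% |
| More than 9 reported units | -0.060 | -0.038 | 0.022/0.060 = 37% |

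The cut on the same answers shrinks even the estimate without baseline.

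**6. Baseline drinking under selection only.** Let the true effect be zero, and let the log-odds of enrolling be 0.5·C·u, with u the drinking trait. Without adjustment the estimate is 0.046, which is spurious; with adjustment it is -0.003. Here the covariate is exactly the trait that drives selection, which flatters adjustment. A further assumed case gave 0.112 without baseline drinking and about 0.063 with it, so (0.112 - 0.063)/0.112 = 44% of the bias was removed.

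**The case against.** The strongest case for the plan is that its adjusted model may be the better one. Hypothesis 6 concerns consumption. Measures defines the baseline items as recall of the past week and past month, so they describe drinking that largely predates the consent page. Adjusting for them cannot remove a real change in later drinking, only a reporting artefact. The mechanism the protocol itself names is differential enrollment, and there adjustment helps (step 6). This stands, and it is why baseline drinking should not simply be dropped. It does not cover the motivational answers, which are not a record of past behavior and which the text could move.

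It is also fair that unadjusted models will be fitted, that baseline characteristics are to be compared among groups, and that Limitations calls the substudies unpowered and exploratory. These points lower the priority. They do not settle which estimate answers hypothesis 6, since the adjusted one is named primary and tested at .05.

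A reader might infer that any consent effect is pulled toward zero by roughly 40%. The documents do not support that. They give no consent effect, the two consent texts sit in an appendix not shown here, and a figure near 40% comes from one assumed mechanism, an equal reporting shift at both times. If the text does not move the answers, nothing is lost.

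**Conclusion.** The structural point holds on the protocol's own sequence. For hypothesis 6 only, the primary model conditions on answers given after exposure to the randomized consent text, and any part of the effect carried by those answers is removed. The loss lies anywhere from none to all.

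The comparison is also restricted to people who consented and were eligible. The intention-to-treat statement fits the main randomization but does not describe this contrast, and no choice of covariates repairs that.

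For baseline drinking there is a trade-off. Including it removes reporting shifts; omitting it leaves selection bias in place. Neither version identifies the effect of the consent mode. For motivation, importance and know-how, the case for leaving them out of the primary model is clearer. All magnitudes rest on assumed inputs. With hypothesis 6 exploratory and unpowered, this is a low-priority correction.

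**What to change.** For hypothesis 6 only:

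- Leave motivation, importance and know-how out of the primary model, and keep sex, age and civil status.
- Present the estimates with and without baseline drinking side by side, saying that the first removes reporting shifts and the second is exposed to selection.
- Keep the full adjustment as a sensitivity analysis.
- Report baseline drinking by consent mode, and say that a difference there may reflect reporting or selection as well as chance.
- Describe the result as a difference between enrolled groups, not as an effect of the consent mode, and exempt this contrast from the intention-to-treat statement.

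The cost is a few sentences of analysis wording, slightly lower precision and one more reported model for an unpowered exploratory hypothesis. No new data are needed, and hypotheses 1 and 7 stay as planned.
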